#### Child Development Accounts

Each child received a US $50 seed deposit to open a dedicated savings bank account, and caregivers were encouraged to make small monthly contributions. Savings of up to US $20 per month (“matching cap”) were matched by project funds at a 2:1 ratio—meaning that for every US $1 saved by the family, the project contributed US $2—and deposited into a separate CDA account managed by the study. These matched savings could only be used toward 3 critical investments essential for family stability and well-being: the child’s education (eg, school expenses and tutoring fees), starting or expanding a small business (eg, a nail salon, animal husbandry, or baking business), or housing improvements. If a family consistently saves US $20 each month for the full 24 months and makes no withdrawals, the total accumulated amount per child would reach US $1490 at the end of the 2-year study. This comprises the US $50 seed deposit, US $480 in family contributions (US $20×24 months), and US $960 in matched funds (US $40×24 months at the 2:1 matching rate).

In Azerbaijan, this amount could cover approximately 1 year of tuition at a private university or a substantial portion of living expenses for a student attending a public university. For younger children, it could fund 1 to 2 years of supplemental educational support, such as tutoring or academic enrichment programs, which are often necessary to prepare for competitive national university entrance examinations. For low-income families, particularly those raising multiple children, accumulating this level of savings is often unattainable without external support.

#### Financial Education

Families participated in 8 weekly 1-hour financial education sessions delivered in groups of 5 families. During each session, caregivers and children attended separate age-appropriate group sessions conducted simultaneously in different rooms. Caregivers’ sessions covered topics such as the importance of saving, sources of income, income generation, family budgeting, and resource management. The curriculum was originally developed by FS, a coinvestigator, and has been implemented with children and families in Sub-Saharan Africa participating in asset-based economic empowerment interventions. Based on the Junior Achievement *More Than Money* program, children participated in 8 weekly interactive, game-based sessions that introduced financial literacy and entrepreneurship concepts in an engaging and age-appropriate format. Through hands-on activities, role-playing, and educational games, children learned practical skills in earning, spending, saving, and money management. The sessions aimed to develop the ability to make informed financial decisions, understand trade-offs associated with spending and saving choices, and explore basic entrepreneurship concepts while identifying how their interests, strengths, and talents can be developed into future educational and career opportunities. Adapted for the Azerbaijani cultural context, the curriculum promotes both financial capability and positive future orientation. Both curricula were tailored to the cultural and economic context of low-income families in Azerbaijan. After completing financial education, families met monthly with a mentor to review their savings progress.

### Usual Care

In addition to the 3 experimental interventions, all participants were eligible to receive standard public services under Azerbaijan’s national deinstitutionalization program for family reunification and reintegration. This included case management, referrals to public schools, and social support services during the transition and reintegration process—such as medical-social services, sociopedagogical support (education and development), and linkage to the general social protection system (financial and material assistance for vulnerable families). The government’s standard support focuses on case management, access to social and medical-psychological services through state institutions, and basic follow-up after reunification. The emphasis is on returning children to a family environment and connecting them to existing public services.

### Intervention Quality Assurance and Implementation Measures

For each component, we will analyze data regarding participation (eligibility, enrollment, and attrition rates), intervention fidelity (via facilitator and participant rating forms completed at the end of each session), safety (number of adverse events), intervention acceptability (participant satisfaction, session attendance, and associations between satisfaction and attendance), perceived usefulness (relevance and utility), and cross-arm contamination.

Two interim analyses will be conducted when 33.3% and 66.7% of the planned sample size have completed 6-month follow-up assessments. With respect to efficacy, if any interim analysis shows statistical significance (*P*<.05) for all primary outcomes, the study will be stopped, indicating a significant benefit of 1 intervention over another. With respect to futility, if the effect size estimates suggest a null result is likely given the planned total sample size, the study may be stopped to conserve resources. A post hoc power analysis will assess the minimum sample size needed to achieve 80% power *and* reject the null hypothesis at each interim analysis. If this exceeds the planned 400 dyads for self-reported outcomes, the investigative team will discuss whether to stop the study for futility or modify the design to avoid it, such as increasing enrollment or hiring additional staff.

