**Results:**

Recruitment occurred between 2022 and 2023, with 2-year follow-up data collection completed in 2025. Intervention effects analyses are ongoing and are expected to be completed in 2026.

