### Data Collection

Children, their caregivers, and their teachers completed surveys at baseline, year-1, and year-2 follow-up. Child and caregiver data were collected through interviewer-administered surveys conducted separately in Azerbaijani by trained graduate-level psychology students serving as RAs. Assessments were conducted at local field offices using iPads and the cloud-based Qualtrics survey platform and required approximately 50 to 60 minutes to complete. Teacher surveys were completed independently. All surveys contained the same scales, except for demographic data that do not vary over time (eg, ethnicity, age). Except for nonverbal digital cognitive tasks (WISC and CANTAB), all instruments were translated into Azerbaijani and tested in a pilot feasibility study. The CANTAB battery consists of simple computer-administered nonlinguistic tasks considered highly precise and largely independent of cultural and language differences [58].

Intervention participation and utilization data (eg, attendance, session completion, and types of services received) were collected from intervention administrative records. Information about children’s academic performance (eg, grades) was collected from school records.

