Aim 1: To estimate the effects of intervention components on child mental health outcomes, differences in outcomes (eg, depression score) will be tested across 3 time points (baseline, 1 year, and 2 years), under an intent-to-treat basis, using linear mixed models. This approach accounts for the autocorrelation of observations nested within individuals over time. We will use logistic functions for binary outcomes (eg, mental health symptoms above the clinical cutoff), Poisson or negative binomial functions for count outcomes (eg, the number of aggressive behaviors), and linear functions for continuous variables (eg, self-esteem score). Statistical inference will be based on F-statistics and their associated *P* values for between-subject effects (the intervention assignment × time terms). To estimate the main effects for the 3 intervention components, we will determine if there is a difference in change across time using the baseline as the reference point (eg, 1 year vs baseline; 2 years vs baseline). We will also include 2-way interactions between components (eg, Family Strengthening by Economic Empowerment by Time interaction). Since we will use effect (–1, 1) coding rather than dummy (0, 1) coding, the power for tests of main effects and interactions will be identical for similarly sized effects. Covariates will include baseline attributes for outcome variables (eg, child’s age and gender, caregiver characteristics).Aim 2: To test which intervention component is mediated by hypothesized mediators, including (1) supportive parenting (eg, quality of child-parent relationships), (2) emotion regulation (eg, self-regulation), and (3) parental stress (eg, stress response). We will use a 2-step process [61] to test (1) a measurement model using confirmatory factor analysis that examines the relationships between the latent constructs and their indicator variables and (2) a structural model to test the hypothesized relationships between the latent mediating and outcome constructs and the intervention [62]. We will use the maximum likelihood method of parameter estimation with missing data. We will also conduct separate analyses to examine the effectiveness of intervention components in specific subgroups (eg, by gender).Aim 3: Qualitative analysis will be conducted in both Azerbaijani and English to explore barriers and facilitators to intervention participation and implementation. Bilingual investigators and 2 additional coders will independently review interview transcripts and conduct thematic analysis [63] and content analysis [64] using Dedoose [65]. Analyses will assess themes and concepts regarding participants’ and intervention facilitators’ perspectives on mental health needs, intervention engagement and acceptability, changes in family relationships and dynamics, and contextual and sociocultural factors influencing intervention delivery and outcomes.

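### The interim analyses are timed on a 6-month assessment that is absent from the described schedule, and their efficacy and futility rules are poorly specified

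*Protocol article*

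**What the plan says.** Under Intervention Quality Assurance and Implementation Measures, the protocol article fixes the timing: "Two interim analyses will be conducted when 33.3% and 66.7% of the planned sample size have completed 6-month follow-up assessments". The efficacy rule is that "if any interim analysis shows statistical significance (*P*<.05) for all primary outcomes, the study will be stopped", and such a stop is read as "indicating a significant benefit of 1 intervention over another". Futility is judged from interim effect estimates: "A post hoc power analysis will assess the minimum sample size needed to achieve 80% power" and reject the null hypothesis. If that number is above the planned 400 dyads for self-reported outcomes, the team discusses whether to stop or to change the design, with larger enrolment given as one example.

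Data Collection gives the schedule: "Children, their caregivers, and their teachers completed surveys at baseline, year-1, and year-2 follow-up". Analytical Strategy, Aim 1, agrees: outcome differences "will be tested across 3 time points (baseline, 1 year, and 2 years"). The Methods paragraph of the abstract lists the same three occasions, and Analytical Strategy places the main effects at 1 and 2 years.

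The abstract reports recruitment in 2022 to 2023, "with 2-year follow-up data collection completed in 2025". The article does not say whether either interim analysis took place.

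**The concern.** A trigger tied to a visit that is not in the schedule cannot be reached, so a reader cannot tell what data, if any, were examined early. This matters because the article presents itself as the record of the prespecified plan before effect results are published. If looks were made on other data, such as year-1 scores, the final tests do not have exactly the stated level. If none were made, the efficacy and futility rules should not stand as part of the plan.

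Three features of the rules also look wrong on their face. The interim threshold equals the full two-sided 0.05, with nothing set aside for the final test. The Benjamini-Hochberg step in Analytical Strategy is given for multiple related hypotheses and does not mention repeated looks. The conclusion attached to stopping is a head-to-head statement that the factorial contrasts do not test. And a sample size recomputed from the observed interim effect restates the interim p-value, so it adds nothing to the interim test as a guide to futility.

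**Working it through.** **Schedule.** The interim paragraph needs 6-month assessments. The abstract, Data Collection, Aim 1 and the last paragraph of Analytical Strategy give baseline, 1 year and 2 years only. No passage supplies a 6-month wave.

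**Planned size.** Power Calculations: 400 × (1 − 0.10) = 360 analysed, which reproduces. The detectable effect of 0.09 to 0.12 is compatible with Cohen's f in standard repeated-measures calculations. The autocorrelations and the type of test are not printed, so it cannot be reproduced exactly, and it is not disputed here.

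**Assumptions for the rest.** Looks at information fractions 1/3, 2/3 and 1; full information at N = 400; normal test statistics with known variance; equally correlated outcomes; clustering within families ignored. The documents give no correlation between outcomes, so r is varied.

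**Efficacy.** For a single outcome tested at |z| > 1.96 at all three looks, simulation gives a type I error of 10.7%. The written rule stops early only if every primary outcome has P<.05 at the same look. For one outcome, type I error is then P(early stop, or |z| > 1.96 at the end) under the global null:

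| Primary outcomes | r | Early stop | Type I error, one outcome |
|---|---|---|---|
| 3 | 0.5 | 0.6% | 5.35% |
| 5 | 0.5 | 0.15% | 5.1% |
| 7 | 0.5 | 0.06% | 5.1% |
| 3 | 0.9 | 3.9% | 7.4% |

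**Comparison.** Study Design (Table 1 and its text) compares groups 1 to 4 with groups 5 to 8 for family strengthening, that is, on versus off. Aim 1 uses effect coding (−1, 1) and component-by-time terms. Neither tests one component against another.

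**Futility.** Let θ be the expected z at N = 400. Power of 80% requires θ = 1.96 + 0.84 = 2.80. With θ̂ the interim effect on that scale, the re-estimated size is N̂ = 400 × (2.80/θ̂)², and N̂ > 400 exactly when |θ̂| < 2.80. At information fraction t, θ̂ has mean θ and SD 1/√t: 1.73 at look 1 and 1.22 at look 2.

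- True effect with 80% power at 400 (θ = 2.80): P(flag) = Φ(0) = 50% at each look. The two estimates have correlation √(1/2) = 0.707, so P(neither flags) = 1/4 + arcsin(0.707)/(2π) = 0.25 + 0.125 = 0.375, and P(at least one flag) = 62.5%. By simulation, 69% of flagged trials would still be significant at the end.
- Effect with 80% power at the planned 360: 46% and 45% at the two looks, 58% over both.
- Effect 25% larger (θ = 3.50, power Φ(3.50 − 1.96) = 94%): Φ(−0.70/1.73) = 34% and Φ(−0.70/1.22) = 28%; 43% over both by simulation.
- True power of 95% or 99% at 400: 40% and 23% over both looks.

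On the interim z scale the flag is |z| < 2.80 × √(1/3) = 1.62 at look 1 and |z| < 2.80 × √(2/3) = 2.29 at look 2, that is, p > .106 and p > .022. At the second look, an outcome with p between .022 and .05 would therefore meet the efficacy threshold and be flagged for futility as well.

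**The case against.** Several stronger readings are tempting, and the documents do not support them.

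- *The type I error is 10.7%.* That belongs to a rule that stops on one outcome. This rule needs all primary outcomes, and Analytical Strategy lists at least five constructs, some with two informants, so the smaller figures in the table are the relevant ones.
- *The futility rule flags working components most of the time.* At the design effect a single look flags half the time. The rate passes half only over both looks, and it falls to 43% for a 25% larger effect and 23% at 99% power.
- *A flag stops the trial.* It opens a discussion, with stopping and redesign both possible. The 69% is therefore not a count of lost trials.
- *Enrolment rose from 400 to 439 because of an interim result.* No passage says so, and several children per family could be enrolled. Had N been raised to 439 under this rule at one look, type I error would be about 5.1%, and 5.1 to 5.3% for the worst data-driven choice.
- *The future tense shows that the looks never happened.* The article describes other planned work in the same tense. Completion of recruitment and follow-up shows only that no rule ended the trial early.

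These points limit the size of the problem. They leave standing the contradictory trigger, the missing allowance for looks, the mismatched comparison, and the weakness of judging futility from the observed effect.

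**Conclusion.** The concern holds in this limited form. The interim timing contradicts the article's own assessment schedule; that rests on the text alone and needs no assumption. The efficacy rule makes no allowance for repeated looks, but the likely cost is small: about 5.1 to 5.4% for one outcome at r = 0.5, and 7.4% in the least favourable case shown (3 outcomes, r = 0.9). The wording of the stopping conclusion does not match the on-versus-off tests. The futility trigger is a coin toss at each look for a component with exactly the 80%-power effect (about 62% over both looks, per outcome), so it is not a sound basis for discussing futility or enrolment. The figures depend on the normal approximation, on taking 400 as full information and, for efficacy, on the assumed correlations. Whether the final p-values are affected at all depends on whether looks were made, which the article does not say.

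**What to change.** Correct the interim paragraph so that it agrees with the assessment schedule and states whether any outcome looks were made.

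- If none were made, say so and withdraw the efficacy and futility rules.
- If any were made, report when, on which data and at which thresholds. Account for those actual looks in the final type I error, alongside the Benjamini-Hochberg control. State whether enrolment above 400 responded to interim effects.
- In either case, describe the comparison as component on versus off.

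An O'Brien-Fleming final threshold should not simply be adopted: it is valid only if the earlier looks used the matching boundaries, and the written rule used P<.05. Designing a new futility rule serves no purpose now that follow-up is complete.

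The cost is a text correction and, only if looks were made, a slightly stricter final threshold.

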### Participant Timeline

Families were recruited in 3 major cities (Baku, Sumgayit, and Ganja). Trained local research assistants (RAs) distributed recruitment materials to recruiters who invited families to join the study. Local research staff provided additional information to interested candidates and obtained informed consent. To minimize potential pressure on children and parents, consent was obtained by a research staff member rather than by representatives of local authorities.

After obtaining informed consent, RAs conducted a screening interview to determine participant eligibility. Potential participants were offered a choice of either US $1 or equivalent nonmonetary compensation (eg, toys, football) for completing the interview. To promote retention, participants provided their addresses, email addresses, and telephone numbers at baseline, along with contact information for at least 3 other individuals who could assist in reaching them. After completing the baseline survey, families were informed of their randomized intervention assignment.

### Randomization

The principal investigator (PI) conducted the randomization prior to the start of recruitment. Eight computer-generated random numbers (ranging from 0 to 100) were assigned to the 8 intervention conditions and ranked from lowest to highest to determine the allocation sequence within each city. The first 5 families recruited in a city were assigned to the first intervention condition in the sequence. After 5 families had been assigned to each intervention condition, allocation resumed at the beginning of the sequence. To reduce predictability, the random numbers were generated from a range of 0 to 100 rather than 1 to 8. A secure, web-based, password-protected database was used to maintain the randomization record.

Data collectors were masked to participants’ intervention group assignments. To foster fidelity to the intervention manuals and maintain the integrity of each separate intervention, facilitators delivered only 1 type of intervention and were not trained in the specific content of the other intervention strategy. Due to the nature of the recruitment procedures, participants could not be blinded to the existence of other intervention conditions.

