## Methods

### Study Design

This randomized clinical trial used a full 2³ (2×2×2) factorial design based on the multiphase optimization strategy (MOST) framework to test and compare three intervention approaches: (1) a family-strengthening intervention, (2) trauma-focused child mental health services, and (3) asset-based economic empowerment via Child Development Accounts (CDAs).

Multicomponent interventions are often tested as “bundles,” making it difficult to disentangle the contributions of individual components. The MOST is a systematic method that allows for the testing of the independent effects of different intervention components to identify their most optimal combination [15]. While multiarm randomized controlled trials are costly, often limited in arms, and require larger sample sizes, the MOST uses a factorial design. By comparing combinations of experimental conditions, the study can have a greater number of conditions without a substantial increase in sample size. This is advantageous in LMICs, where it is essential to implement only the most efficacious aspects of a program. The MOST consists of three phases: (1) preparation, (2) optimization, and (3) evaluation of the optimized intervention in a randomized controlled trial [16]. This study falls within the optimization phase.

This study includes 3 factors—the intervention approaches—each with 2 levels (delivered/“on” or not delivered/“off”). This is a full 2×2×2 factorial design, meaning that the study has 8 different experimental conditions or groups (2^3^=8) [17]. Child-parent dyads (n=439) were randomly assigned to 1 of 8 groups (about 54 dyads per group), which determined the combination of interventions they received. Given this design, half of the sample (n≈220) received each intervention (eg, families assigned to groups 1‐4 received the family-strengthening intervention and were compared with families from groups 5‐8; Table 1).

**Table 1. T1:** Experimental conditions^a^.

Group	Usual care	Experimental interventions		
	Standard deinstitutionalization program	Family strengthening	Trauma-focused mental health services	Economic empowerment
1	On	On	On	On
2	On	On	On	Off
3	On	On	Off	On
4	On	On	Off	Off
5	On	Off	On	On
6	On	Off	On	Off
7	On	Off	Off	On
8	On	Off	Off	Off

a Child-parent dyads (n=439) are randomly assigned to 1 of 8 experimental conditions (~54 dyads per group), determining how many and which intervention components participants receive.

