### Intervention A: Family Strengthening

This study uses an adapted version of the family-strengthening intervention “SAFE Children” to improve child-parent relationships, enhance supportive parenting strategies, and prevent emotional and behavioral problems among at-risk children [23]. SAFE Children was initially designed for at-risk families from low-income US neighborhoods and uses a multi-family group approach to build social support. Including multiple families is an efficient service delivery model, fostering support among participants and improving parent-child interactions directly [35].

Families participated in 12 weekly sessions, with themes including identifying family strengths, developmental expectations, communication skills, behavior management, parental distress management, and conflict resolution. The adapted intervention incorporates topics that address unique issues faced by families during reunification (eg, attachment issues, children’s feelings of resentment, parental guilt, and shame). In response to the findings of the pilot study, sessions were offered on weekends to accommodate families’ schedules. The intervention developer and coinvestigator ([name]) oversaw the training and intervention adaptation process to ensure fidelity to its core components. The intervention is delivered in multifamily groups of 5 families. Children and caregivers attend sessions together, separating into child- and caregiver-specific activities only when required by the curriculum. To strengthen family engagement and reinforce skills at home, all household members involved in child-rearing are encouraged to participate, including siblings who do not meet study eligibility criteria.

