
In the data analysis, the primary outcomes include children’s mental health and socioemotional functioning. Secondary outcomes include cognitive and social processes associated with mental health, as well as functional outcomes related to academic performance and social functioning in the school setting. Specifically, primary mental health outcomes include child-reported depressive symptoms, posttraumatic stress symptoms, and self-esteem; caregiver- and teacher-reported ADHD symptoms and general socioemotional functioning such as internalizing and externalizing problems; and clinician-administered mental health outcomes among families randomized to the mental health services condition. Secondary outcomes include child cognitive functioning, assessed using WISC-V and CANTAB tasks; child-reported social support, particularly peer support; and teacher-reported grades and school behaviors. Mediating variables include caregiver-reported parenting practices, caregiver mental health, family functioning, coping strategies, social support, saving attitudes, and household economic well-being.

The main analyses focus on treatment effects at the 1-year and 2-year follow-ups, with the 1-year follow-up used to assess initial intervention effects and the 2-year follow-up used to assess the maintenance of those effects over time. Children from the same family will be accounted for using mixed-effects models, with random effects specified to adjust for the nonindependence of observations among children nested within the same family. Missing outcome data will be handled using maximum-likelihood estimation under a missing-at-random assumption, with sensitivity analyses using multiple imputation. To address the multiple testing issue, we will control the false discovery rate using the Benjamini-Hochberg procedure [66,67]. This approach was selected instead of Bonferroni correction because it limits false discoveries while avoiding the overly conservative loss of power associated with Bonferroni adjustment when multiple related hypotheses are tested.

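### Conditions were allocated to batches of five consecutive families within a city, but the stated model accounts only for repeated measures and siblings, so component × time standard errors are too small if change is correlated within batches

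*Protocol article*

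**What the plan says.** **Allocation.** In the Randomization section, random numbers put the eight conditions in order within each city. Then "The first 5 families recruited in a city were assigned to the first intervention condition in the sequence", and "After 5 families had been assigned to each intervention condition, allocation resumed at the beginning of the sequence". No separate draw for a family or a dyad is described.

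**Design statement.** The Study Design section says "Child-parent dyads (n=439) were randomly assigned to 1 of 8 groups".

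**Model.** Under Analytical Strategy, Aim 1 uses mixed models over baseline, 1 year and 2 years, and inference rests on the intervention × time terms. On repeated measures it says "This approach accounts for the autocorrelation of observations nested within individuals over time". Later in the same section siblings are covered, "with random effects specified to adjust for the nonindependence of observations among children nested within the same family". No term for the allocation batch is stated.

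**Delivery.** For family strengthening, "The intervention is delivered in multifamily groups of 5 families". For the economic component, "Families participated in 8 weekly 1-hour financial education sessions delivered in groups of 5 families". Mental health sessions are typically individual.

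**The concern.** A trial should be analysed at no finer level than the one at which conditions were assigned. Here every component contrast compares whole batches with whole batches, while the stated random effects stop at the family, one level below. Families in a batch were recruited one after another in the same city, so they share a recruitment period. Where a condition includes family strengthening or economic empowerment (conditions 1–5 and 7 in Table 1), they probably also share group sessions, because the group size equals the batch size.

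If either makes children in a batch change alike, the model counts more independent information than there is. The resulting p-values feed the Benjamini-Hochberg step, which presupposes valid p-values and cannot repair ones built on understated errors. The purpose of the trial is to decide which components belong in the optimized package, so a false positive would mean keeping a component that does nothing.

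**Working it through.** **The plan's own figure.** Power Calculations gives a detectable effect size of 0.09 to 0.12 with 360 analysed children, two-sided 5% and 80% power. Read as Cohen's f for a two-group, three-visit between-factor test, with noncentrality f² × 360 × 3 / (1 + 2ρ), it is reproduced as 0.094 at ρ = 0.1 and 0.121 at ρ = 0.5. The match is not unique, because the two ρ values are not stated. It treats the 360 children as independent, with no family or batch term.

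**Inputs from the Results section.** 439 children and 305 caregivers, of whom 107 have more than one child enrolled. Taking one family per caregiver and full batches:
- batches: 305 / 5 = 61
- children per family: c = 439 / 305 = 1.44
- children per batch: M = 439 / 61 = 7.20

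**Assumed, because the document gives no ICC.** Correlation of change from baseline within a family (ICC_f) of 0.2 to 0.4, and between families in the same batch (ICC_b) of 0.01 to 0.10. Change is the right scale because the tested terms are intervention × time; a batch effect that is constant over visits largely cancels.

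**Method 1, design effects.**
- Family only: D0 = 1 + (c − 1) × ICC_f
- Family and batch: D1 = D0 + (M − c) × ICC_b
- Standard-error ratio: R = √(D1/D0)
- Actual two-sided level: 2 × [1 − Φ(1.96/R)]

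Example with ICC_f = 0.2 and ICC_b = 0.05: D0 = 1 + 0.44 × 0.2 = 1.09; D1 = 1.09 + 5.76 × 0.05 = 1.38; R = 1.125; level = 8.1%.

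**Method 2, allowing for unequal family sizes.** There are 305 − 107 = 198 single-child families, and 439 − 198 = 241 children in the other 107. If these are 80 pairs and 27 triples (160 + 81 = 241), the size-weighted family size is (198 + 320 + 243)/439 = 1.73. With ICC_f = 0.30 and ICC_b = 0.05, the variance of a batch mean is:
- true: 0.05 + 0.25 × 1.73/7.2 + 0.70/7.2 = 0.207
- family-only: 0.30 × 1.73/7.2 + 0.70/7.2 = 0.169
- ratio: 1.22, so the model understates the variance by 1 − 1/1.22 = 18%, and the level is 7.6%

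| Batch ICC of change | SE ratio, method 1 | Level, method 1 | Level, method 2 | Variance ratio, method 2 | Variance understated, method 2 |
|---|---|---|---|---|---|
| 0.01 | 1.02–1.03 | 5.6% | 5.5% | 1.04 | 4% |
| 0.02 | 1.05 | 6.1–6.2% | 6.0% | 1.09 | 8% |
| 0.05 | 1.12–1.13 | 7.9–8.1% | 7.6% | 1.22 | 18% |
| 0.10 | 1.22–1.24 | 10.8–11.3% | 10.3% | 1.45 | 31% |

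**Simulation check.** Change scores were simulated under the null with 61 batches of five families, a rotating order in three cities, eight conditions, batch correlation in all conditions and a family-only fit (6,000 runs per setting). Rejection rates were about 5% at batch ICC 0, then 6.2–6.3%, 7.9–8.3% and 11.3–11.6% at 0.02, 0.05 and 0.10.

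**The case against.** The strongest reply is that the size is unknown and may be nil. The inflation needs a positive batch correlation in change, the document gives none, and at 0.01 the effect is trivial. That stands. It is a reason to let the analysis allow for batch variance, not to set it to zero.

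A second reply is that the article is condensed and the sentence on siblings need not list every random effect. This has some force. But the article does name the levels of dependence it handles and, in Study Design, describes a unit of allocation that its own Randomization section contradicts. A reader following the text as written would omit the batch.

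Several stronger readings are tempting and are not supported:
- **That the batches are the delivery groups, or share a facilitator or recruitment source.** No section says so. The equal size of five families makes shared groups likely in conditions 1–5 and 7. Conditions 6 and 8 contain no group-delivered component.
- **That a family random intercept cancels from the time contrast and so gives no protection.** The article says random effects, without limiting them to intercepts.
- **That the absence of a city term is an error.** The covariate list is open-ended, and such detail may sit in an analysis plan not shown here.

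**Conclusion.** The point holds in conditional form. The allocation unit is a batch of five families in all eight conditions; the stated model stops at the family; and the two descriptions of what was randomized conflict. None of this depends on the delivery-group inference.

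Standard errors for component × time are too small whenever change is positively correlated within batches. A reader might go further and conclude that every component's p-value is certainly too small. The documents do not support that: no ICC of change is given, and for mental health services there are no shared therapy sessions, so the argument for that component leans more on shared recruitment period. Under the assumed range the nominal 5% level becomes about 5.6% to 11%, negligible at a batch ICC of 0.01 and material from about 0.05. These figures assume full batches, one family per caregiver and batch correlation in all conditions.

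The article reports that effect analyses are still ongoing, so the correction can still be made.

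**What to change.** 1. In the mixed model under Analytical Strategy, account for the five-family allocation batch in the component × time tests. Either add batch and batch-by-visit random effects with small-sample degrees of freedom, or use batch-clustered standard errors with a small-sample correction. The second route is simpler for binary and count outcomes. A batch intercept alone is not enough, because it largely cancels from the time contrast.
2. Include city as a fixed effect, since the sequence was drawn within city. With 61 batches, eight conditions and three cities, about 61 − 8 − 2 = 51 batch-level degrees of freedom remain.
3. Correct Study Design, including the note to Table 1, to say that batches of five families were assigned.
4. Optionally, check the main results with a randomization test that re-draws the condition order within each city.

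**Cost.** No new data collection, but batch membership must be recovered from the randomization record. Over the assumed ICC range standard errors rise by roughly 2–24%. A test with 80% power under the family-only standard error would then have about 78% at a batch ICC of 0.01, 70–71% at 0.05 and 62–63% at 0.10.
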